##### MRI reporting

VI-RADS provides a systematic method for reporting bladder MRI results, incorporating T2-weighted imaging, diffusion-weighted imaging (DWI) and dynamic contrast enhancement (DCE) to determine the likelihood of muscle invasion. In VI-RADS, the probability of muscle invasion is assessed using a 5-point scale. A VI-RADS 1 score indicates a highly unlikely occurrence of muscle invasion. With a VI-RADS 2 score, muscle invasion is unlikely. With a VI-RADS 3 score, the presence of muscle invasion becomes equivocal. A VI-RADS 4 score indicates that muscle invasion is likely. And a VI-RADS 5 score signifies a very likely invasion of the muscle, extending beyond the bladder.

##### Central radiology review

Double-readings of the mpMRI scans will be performed at the main investigator’s location (Radboudumc) by a dedicated team of radiologists. In case of discrepancies, a third independent reader at the main investigator’s location will be consulted. Each reader will be blinded to the other’s assessments before finalising conclusions on VI-RADS. After reaching consensus, the final result will be reported to the patient’s urologist. In addition, the inter-reader variability among radiologists will be assessed by calculating the intraclass correlation coefficient.

##### Same-day biopsy

Histological confirmation of urothelial carcinoma will be obtained through an outpatient bladder biopsy procedure performed on the same day. A small tumour fragment will be collected using a cold cup biopsy device during cystoscopy.

##### Treatment and follow-up

Results from the mpMRI and biopsy are discussed in a multidisciplinary tumour board, where definitive treatment plans will be determined. Patients with a VI-RADS score of 1 or 2 will be classified as having NMIBC and will typically undergo TURBT, often supplemented by bladder instillations and/or re-TURBT. Those with a VI-RADS score of 3, 4 or 5 will be classified as having MIBC and will undergo definitive treatment, usually involving RC with or without NAC or chemoradiotherapy.

After treatment, all patients, including those in the standard care arm, will be monitored and progression will be assessed by imaging: (PET-)CT every 6 months until the third year, followed by an annual CT scan thereafter. The minimum follow-up duration for all participants in the study is 2 years from the point of randomisation. It is anticipated that patients enrolled earlier in the study can be monitored for a longer duration, potentially to 4.5 years, compared with those who enrol later.

##### Pathology review

All resected specimens from TURBT and cystectomy will be evaluated and reported by a urogenital pathologist, following standard protocols. At the end of the study, all specimens from the intervention arm—those obtained from TURBT (when mpMRI suggests NMIBC) and RC (without NAC, when mpMRI suggests MIBC)—will undergo central review to assess the diagnostic validity of mpMRI.

It is anticipated that mpMRI will classify a maximum of 10% of patients as NMIBC, who will then undergo TURBT. The remaining 90% of patients will be classified as MIBC, with approximately two-thirds of them treated with RC alone. As a result, a central pathology review will be conducted for approximately n=120 cases. As the central pathology review is performed at the end of the trial, results do not affect the choice of definitive treatment.

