**Methods and analysis:**

BladParadigm is a two-arm multicentre randomised controlled trial (RCT) conducted in the Netherlands. Over a 3-year period, patients with clinically suspected MIBC without evidence of metastases will be recruited and randomised 1:1 to either TURBT or 3-Tesla mpMRI with same-day outpatient bladder biopsy. The Vesical Imaging Reporting and Data System (VI-RADS) will be used to standardise mpMRI reporting. Patients will undergo definitive treatment based on the results of the TURBT or mpMRI. The study is powered to demonstrate that the mpMRI-based strategy is at least non-inferior to standard TURBT in patients treated with radical cystectomy alone, assuming a relative hazard of 0.55. The required sample size is 360 patients (180 TURBT, 180 mpMRI). The primary outcome is 2-year progression-free survival. Progression will be assessed by imaging, according to the current standard of care. Secondary outcome measures are time to definitive treatment, quality of life (EuroQol 5D-5L), healthcare costs and cost-effectiveness.

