## Introduction

### Background and rationale

 Organ-confined muscle-invasive bladder cancer (MIBC) is one of the very few types of cancer for which the prognosis has not improved for decades. Despite receiving curative treatment, around 50% of patients will die from the disease within 5 years.^1^ This indicates that in many cases, the cancer has already spread at the time of radical treatment, even though imaging techniques show no signs of metastasis.

Transurethral resection of the bladder tumour (TURBT) is the current standard for both pathological confirmation and local staging of bladder cancer, but it has several limitations. Unlike most cancers, which are staged non-invasively through imaging, bladder cancer requires TURBT, an invasive procedure that involves cutting through the tumour and its surrounding vasculature, potentially leading to tumour cell dissemination. Small studies have demonstrated the presence of circulating tumour cells (CTCs) in the blood following TURBT, supporting the hypothesis of procedure-induced tumour cell spread.^2^,^4^ Additionally, TURBT may underestimate muscle invasion due to inadequate sampling and tissue handling, necessitating re-TURBT in up to 30% of cases.^5^,^8^ These limitations may delay definitive treatment and contribute to the persistently poor prognosis of MIBC, despite advances in curative therapies.^9^

In the past decade, multiple studies have shown that multiparametric MRI (mpMRI) can be an effective non-invasive imaging tool for assessing detrusor muscle invasion in patients with bladder cancer. Meta-analyses have reported high sensitivity (83–90%) and specificity (88–90%) for mpMRI.^10^,^12^ A recent UK-based trial (BladderPath)^13 14^ introduced an MRI-directed diagnostic pathway for patients with suspected MIBC and showed that it is feasible to incorporate mpMRI into the diagnostic pathway for patients with bladder cancer, and this led to a significant reduction in time to correct treatment. However, since oncological outcomes such as progression-free survival (PFS) were not evaluated, the BladParadigm trial is designed to evaluate whether an mpMRI-based approach can safely replace TURBT in terms of both effectiveness and costs.

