Another methodological consideration is the use of VI-RADS 3 as a threshold for classifying patients as MIBC. In the original VI-RADS paper, a score of 3 is considered equivocal.^16^ While more recent studies report high diagnostic performance for VI-RADS≥3—with sensitivities of 87–91% and specificities of 82–97%^12 28 29^—the risk of overtreatment in non–muscle-invasive cases cannot be entirely excluded. A meta-analysis by Woo *et al* (n=1170) found a sensitivity and specificity of 92% and 84% for VI-RADS 3–5, compared with 72% and 96% for VI-RADS 4–5, respectively. Although a higher cut-off would reduce false positives, we chose to include VI-RADS 3 in the MIBC category for two reasons. First, the pre-test probability of MIBC in our study population is high (72–78%) because patients are only included if cystoscopy suggests a high likelihood of muscle invasion (Likert score 4 or 5). In this context, the positive predictive value of VI-RADS 3–5 rises to 93.6–95.4%. Second, although inter-reader variability in mpMRI interpretation remains an inherent limitation, the use of central double reading with consensus reporting is expected to improve consistency and reduce the number of equivocal (VI-RADS 3) classifications.

We acknowledge that overstaging may lead to overtreatment, particularly in patients with large, aggressive-looking tumours that may still be non-muscle-invasive. In clinical practice, however, such tumours are often treated more aggressively regardless of histological confirmation, and radical cystectomy is not uncommon in these cases. Although there is no direct evidence quantifying overtreatment in this context, we estimate that its occurrence is low—likely below 5%—corresponding to a positive predictive value above 95%. Conversely, if mpMRI understages an MIBC case and incorrectly classifies it as NMIBC, the patient will still undergo TURBT as per protocol, allowing for detection of muscle invasion at that point. In such cases, the primary consequence could be a delay of several days due to the initial mpMRI and biopsy procedure.

Notwithstanding these limitations, if the results of this RCT show that this new diagnostic approach combining mpMRI with a same-day bladder biopsy is a reliable, safer, faster and more economical alternative for local staging of bladder cancer compared with TURBT, it will pave the way for a paradigm shift in bladder cancer staging.

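### The reference for mpMRI's diagnostic validity depends on the mpMRI result: taking TURBT as truth for VI-RADS 1–2 overstates NPV and specificity, with uncertain net effect on sensitivity

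*Protocol article*

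**What the plan says.** The Pathology review section of the protocol article names the intervention-arm specimens for central review: "those obtained from TURBT (when mpMRI suggests NMIBC) and RC (without NAC, when mpMRI suggests MIBC". It gives the purpose: they "will undergo central review to assess the diagnostic validity of mpMRI". No accuracy measure is named. The section expects that "mpMRI will classify a maximum of 10% of patients as NMIBC", that about two-thirds of the remaining patients will have cystectomy alone, and that about 120 cases will be reviewed.

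Three other places bear on the choice of reference:

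- Background and rationale, in arguing for the trial: "TURBT may underestimate muscle invasion due to inadequate sampling and tissue handling, necessitating re-TURBT in up to 30% of cases".
- Treatment and follow-up: patients with VI-RADS 1 or 2 "will typically undergo TURBT, often supplemented by bladder instillations and/or re-TURBT". Re-TURBT is frequent but not universal.
- Discussion, on MIBC that mpMRI calls NMIBC: "the patient will still undergo TURBT as per protocol, allowing for detection of muscle invasion at that point".

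Diagnostic validity is not among the primary or secondary outcomes, but the strengths and limitations list mentions the central review.

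**The concern.** The source of histological truth is decided by the test under evaluation. mpMRI-positive patients are judged against the cystectomy specimen. mpMRI-negative patients are judged against TURBT, whose failure to show muscle invasion is one of the article's reasons for running the trial. Central re-reading can correct a misread slide, but it cannot find muscle that was never sampled.

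In mpMRI-negative patients this error runs one way. A muscle-invasive tumour missed by both mpMRI and TURBT is entered as a true negative for mpMRI. In addition, cystectomy specimens are listed only for patients whose mpMRI suggested MIBC. On the plain wording, an mpMRI-negative patient whose invasion is first shown at a later cystectomy does not bring that specimen into the review.

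At stake is how far the reported NPV and specificity of mpMRI can be trusted in a population selected for a high suspicion of MIBC.

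**Working it through.** **Inputs.** Intervention arm 180 (Abstract: "The required sample size is 360 patients (180 TURBT, 180 mpMRI"). Sensitivity 92% and specificity 84% for VI-RADS 3–5, with MIBC prevalence 72–78% (Discussion). Share of mpMRI-positives with cystectomy alone: about two-thirds (Pathology review) or 65% (Sample size). The share of mpMRI-negative MIBC that TURBT also misses, *m*, is not given. I assume 10–30%. The re-TURBT figure of up to 30% serves only as a convenient upper end; it is a repeat-procedure rate, not a miss rate.

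**The article's own figures first.**

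- Review size: 180 × 0.10 + 180 × 0.90 × 0.65 = 18 + 105.3 = 123.3. With two-thirds it is 18 + 108 = 126. Both fit a stated size of approximately 120.
- PPV at 72%: 0.92 × 0.72 / (0.92 × 0.72 + 0.16 × 0.28) = 93.7%. At 78% it is 95.3%. The article states 93.6–95.4%.

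**Expected true counts out of 180.**

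- Prevalence 72%: TP 119.2, FN 10.4, TN 42.3, FP 8.1.
- Prevalence 78%: TP 129.2, FN 11.2, TN 33.3, FP 6.3.

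**Bias model.** Let *v* be the share of mpMRI-positives with a reviewed specimen, taken as equal for true and false positives.

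- Observed NPV = (TN + *m*·FN) / (TN + FN). The excess over the truth is *m* × (1 − true NPV).
- Observed sensitivity = *v*·TP / (*v*·TP + (1 − *m*)·FN).
- Observed specificity = (TN + *m*·FN) / (TN + *m*·FN + *v*·FP).

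Results in per cent; paired values are for prevalence 72% / 78%:

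| *m* | NPV | Sensitivity, all positives verified | Sensitivity, *v* = 2/3 | Specificity, all positives verified | Specificity, *v* = 2/3 |
|---|---|---|---|---|---|
| 0 | 80.3 / 74.8 | 92.0 | 88.5 | 84.0 | 88.7 |
| 10% | 82.3 / 77.3 | 92.7 | 89.5 | 84.3 / 84.4 | 89.0 / 89.1 |
| 20% | 84.3 / 79.8 | 93.5 | 90.6 | 84.6 / 84.9 | 89.2 / 89.4 |
| 30% | 86.2 / 82.3 | 94.3 | 91.6 | 84.9 / 85.3 | 89.4 / 89.7 |

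**NPV.** The excess runs from 0.10 × 19.7 = 2.0 points to 0.30 × 25.2 = 7.6 points.

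**Specificity.** It is too high throughout. Most of the excess in the planned review set (84.0% to 88.7%) comes from unverified positives. The TURBT reference adds up to about one point more.

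**Sensitivity.** Observed exceeds true only if *v* > 1 − *m*, that is *m* > 1 − *v*: above 33% for *v* = 2/3 and above 35% for *v* = 0.65. Over *m* = 10–30% with *v* = 2/3, the uncorrected figure is 2.5 to 0.4 points too low.

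**Patients affected.** The accuracy figures above imply 44 to 53 mpMRI-negatives, whereas the Pathology review section expects at most 18. For a given true NPV the bias in points is the same either way, but the count is not. Applying the NPVs above to 18 patients gives 18 × 0.197 = 3.5 to 18 × 0.252 = 4.5 false negatives, of which 10–30% is 0.4 to 1.4 patients. One patient moves NPV by 1/18 = 5.6 points. The approximate 95% half-width, 1.96 × √(NPV(1 − NPV)/18), is 18 to 20 points.

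**The case against.** The strongest opposing case has four parts.

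First, the consequence is small. Diagnostic validity is not a listed outcome, PFS is unaffected, and with 18 mpMRI-negatives the sampling error dwarfs a bias of 2 to 7.6 points. This stands and sets the weight of the point.

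Second, the limitation is partly unavoidable, because patients classed as NMIBC do not routinely have a cystectomy. That also stands. It is a reason for stating bounds, not for treating TURBT as error-free.

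Third, the text may be read more generously. TURBT specimens may naturally include re-TURBT, and every cystectomy is reported by a urogenital pathologist, so a later report would exist. This is fair, and re-TURBT would lower *m*. It does not bring a later cystectomy in an mpMRI-negative patient into the review as worded.

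Fourth, the rules for combining specimens could sit in the full protocol or SAP, which are not shown. Details could. But the article itself fixes which specimens are reviewed for which mpMRI result, and that allocation is the source of the bias.

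Stronger readings are tempting and not supported. A reader might infer that sensitivity is overstated too. The TURBT reference alone does push it up, but the same sentence leaves about a third of mpMRI-positives unverified, which pulls it down by more over the assumed range. A reader might also take the 30% re-TURBT figure as a TURBT miss rate; the article does not say that. Nor does the review underpin omitting TURBT after a negative mpMRI: VI-RADS 1–2 patients typically have TURBT anyway, and the figure the Discussion uses to defend its threshold is PPV, which the TURBT reference does not alter.

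**Conclusion.** The point holds, as a minor one. The reference standard differs by mpMRI result, and the one used for mpMRI-negatives is a procedure the article itself describes as liable to miss muscle invasion. NPV is overstated for any miss rate above zero. Specificity is overstated as well, at 89.0–89.7% in the planned review set against 84.0%, chiefly through partial verification of positives. The net direction for sensitivity cannot be fixed from the document.

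These sizes rest on the Discussion's accuracy and prevalence figures, on the assumed 10–30% for *m*, and on verified positives being representative of all positives. Re-TURBT would lower *m*; tumours that are hard for both tests would raise it. The expected number of misclassified patients at the planned 18 negatives is about one or fewer. The randomised comparison is not affected.

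**What to change.** Amend the Pathology review section, and the analysis text that goes with it, as follows:

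- For VI-RADS 1–2 patients, define the reference as the highest stage across the TURBT, any re-TURBT and any cystectomy without prior NAC within a fixed window after mpMRI. Use existing specimens or reports whatever the mpMRI class. Set the window in advance, since a long one would let later progression pass for missed invasion.
- Class a TURBT without detrusor muscle and without re-TURBT as unverified, not as NMIBC.
- Report NPV, specificity and sensitivity with bounds over a stated range of TURBT miss rates.
- Account for mpMRI-positives without a reviewable cystectomy specimen when reporting sensitivity and specificity, for example with a verification-bias correction, and state its assumptions.

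The review takes place at the end of the trial, so the definition can be changed before it is applied. No patient has an extra procedure and no treatment decision changes. The cost is wording, a few more existing specimens or reports, slightly lower precision as some patients become unverified, and probably a less favourable NPV.

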### Outcomes

#### Primary outcome

The primary outcome is progression-free survival (PFS) at 2 years after diagnosis. PFS is defined as the time between randomisation and the occurrence of distant metastases, nodal recurrence or death from any cause, whichever occurs first. Patients without evidence of progression will be censored at the last date of assessment. In addition to PFS, time to progression (TTP), defined as the time between randomisation and diagnosis of distant metastases or loco-regional nodal recurrence, will be analysed as well. For TTP, we consider death from any cause as a competing risk.

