### Sample size

The power calculation is based on an intention-to-treat (ITT) time-to-event analysis comparing PFS between the randomisation groups. The following parameters were used: alpha two-tailed=0.05, beta (1-power)=0.20 and 1:1 randomisation. Assuming a relative hazard of 0.55, 88 events are needed. With a baseline event rate of 0.23 per year in the TURBT group, a censoring rate of 0.1 per year, and an average follow-up period of 3.25 years, 117 participants are needed in each group. Despite the fact that adding NAC to RC only provides a 5–8% increase in overall survival after 5 years compared with RC alone, the presence of NAC (or chemoradiotherapy) might still alter the impact of TURBT on prognosis. Therefore, we will conduct a stratified analysis on RC alone vs other (systemic) treatment with curative intent. In the Netherlands, less than 15% of patients with cT2-4aN0M0 MIBC are treated with chemoradiation, a little over 20% with NAC and ~65% with RC alone. That means that 117/0.65=180 patients are needed in each arm. This sample size will provide us with the necessary power to analyse our primary research question in RC-alone patients effectively.

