To the best of our knowledge, the BladderPath study is the only other trial that is investigating an mpMRI-based diagnostic pathway for bladder cancer staging. Results on feasibility and time to correct therapy were recently published.^13 14^ The introduction of an MRI-based diagnostic approach led to a 45-day reduction in time to correct therapy. The findings from this study emphasise the importance of staging patients suspected of MIBC with mpMRI rather than TURBT. However, survival data were not evaluated due to insufficient enrolment due to the COVID-19 pandemic. To optimise our study design, we have consulted with the principal investigator of the BladderPath trial and made several adaptations, including the use of a 3T mpMRI (instead of a 1.5T mpMRI as done in the UK trial), evaluating PFS at 2 years after randomisation as our primary endpoint, and a more stringent selection of only patients with a suspicion of MIBC (Likert score 4 or 5 during cystoscopy, instead of all patients with gross haematuria). The latter, however, could also be considered a limitation, as cystoscopic-based assessment of potential muscle invasion is subject to variability and potential inaccuracies. This was shown in two studies on accuracy of cystoscopy where the prevalence of MIBC among patients with a Likert score of 4 or 5 was 72% and 78%, respectively.^26 27^

Equal to the BladderPath trial, follow-up will be at least 2 years for all patients. Given that most patients who experience progression will have progression in the first 2 years after radical treatment, 2 years is a sufficiently large time window for follow-up. It would be of added value to extend follow-up in this trial beyond 2 years to evaluate long-term results, but due to feasibility constraints, this was not possible. Patients will, however, be monitored long-term according to standard of care.

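### The primary outcome is labelled 2-year PFS, but the sample size and log-rank test rest on all follow-up (average 3.25 years), and the protocol does not say which governs

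*Protocol article*

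**What the plan says.** On the horizon, the Primary outcome section reads "The primary outcome is progression-free survival (PFS) at 2 years after diagnosis". The Abstract and Objectives also name 2-year PFS, and the Discussion describes "evaluating PFS at 2 years after randomisation as our primary endpoint". The Discussion adds that it would be valuable to "extend follow-up in this trial beyond 2 years to evaluate long-term results, but due to feasibility constraints, this was not possible".

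Other sections point to longer follow-up. The Sample size section works with "alpha two-tailed=0.05, beta (1-power)=0.20 and 1:1 randomisation", a relative hazard of 0.55 and 88 events, and then with "an average follow-up period of 3.25 years, 117 participants are needed in each group". The Treatment and follow-up section sets a 2-year minimum and expects early entrants to be followed "potentially to 4.5 years, compared with those who enrol later". The Participant timeline runs follow-up over months 7 to 66. For censoring, the Primary outcome section says: "Patients without evidence of progression will be censored at the last date of assessment". Statistical methods plans Kaplan-Meier curves and a log-rank test and gives no 2-year truncation.

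On the time origin, the first sentence of the Primary outcome section counts from diagnosis, but the next says "PFS is defined as the time between randomisation and the occurrence of distant metastases, nodal recurrence or death from any cause".

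**The concern.** A fixed 2-year endpoint and a time-to-event comparison over all follow-up are different analyses with different event counts. The endpoint wording points to the first; the censoring rule, the test and the sample size point to the second. No sentence says whether, for example, a metastasis at month 30 counts in the primary analysis.

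Two things are at stake. First, the 80% power claim was derived for the longer horizon and does not carry over to the shorter one in the set it refers to. Second, participants and treating physicians are not blinded, and the published text would support either a 2-year estimate or a full-follow-up hazard ratio as the primary result. The two can disagree, so the choice should not remain open once data exist.

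**Working it through.** **Inputs (all from Sample size):** hazard ratio 0.55; two-sided alpha 0.05; power 80%; event rate 0.23 per year with TURBT, hence 0.55 × 0.23 = 0.1265 per year with mpMRI; censoring rate c = 0.1 per year; average follow-up 3.25 years, which is the midpoint of 2 and 4.5; 117 per group treated by radical cystectomy (RC) alone; 117/0.65 = 180 randomised per arm.

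**Formulas**
- Required events (Schoenfeld): D = 4(1.960 + 0.842)² / (ln 0.55)²
- Event probability by time t under constant rates: p(t) = h/(h + c) × [1 − exp(−(h + c)t)]
- Power with D events: Φ(√(D/4) × 0.5978 − 1.96), where 0.5978 = |ln 0.55|

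**Reproducing the protocol's figures, t = 3.25**
- D = 87.84, rounded up to 88, as stated.
- p = 0.23/0.33 × (1 − e^−1.0725) = 0.4585 (TURBT) and 0.1265/0.2265 × (1 − e^−0.7361) = 0.2910 (mpMRI).
- 88/(0.4585 + 0.2910) = 117.4 per group, against 117 stated. With 117 per group the expected count is 87.7.
- Spreading follow-up evenly over 2 to 4.5 years, instead of using the midpoint, gives 86.5 events. The calculation therefore stands on the all-follow-up reading.

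**Same inputs cut at t = 2**
- p = 0.23/0.33 × (1 − e^−0.66) = 0.3367 and 0.1265/0.2265 × (1 − e^−0.453) = 0.2035; sum 0.5402.
- RC-alone set: 117 × 0.5402 = 63.2 events, 72% of 88. Power = Φ(√(63.2/4) × 0.5978 − 1.96) = 66%.
- Comparing Kaplan-Meier estimates at 2 years instead: e^−0.46 = 63.1% against e^−0.253 = 77.6%, a difference of 14.5 points with Greenwood SE 6.2 points; power about 65%.
- 88 events by 2 years would need 88/0.5402 = 163 RC-alone patients per group, or 163/0.65 = about 251 randomised per arm.

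**Sensitivity at 2 years**
- No loss to follow-up (c = 0): 69.3 events, 70% power in the RC-alone set.
- All randomised patients, 180 per arm at the same rates: 180 × 0.5402 = 97.2 events, 84% power.
- Front-loaded hazard: the protocol gives no time-varying rate. If the 3.25-year total of 87.7 is held fixed, the 2-year count lies between 63.2 (constant rate) and 87.7 (every event within 2 years).

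**The case against.** The strongest reply is that no analysis is ever said to stop at 2 years. Censoring is at last assessment, the log-rank test has no cut-off, follow-up is scheduled to month 66, and the sample size is described as a time-to-event calculation. Read that way, 2-year PFS is a loose label, 117 per group gives 87.7 events, and no stated sum is wrong. The Discussion's remark can also be read mildly: its paragraph opens with a 2-year minimum for everyone, so what was not feasible may be extending that minimum. The data cut-off may be fixed in the analysis plan, which was not available here.

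Much of this stands. A reader might infer that the trial is simply underpowered for its primary outcome. The documents do not support that: the shortfall depends on truncation at 2 years and is confined to the RC-alone set, and the full intention-to-treat comparison would keep about 84% power even then. The Discussion also says that most patients who progress do so within 2 years of radical treatment, so 63 may be too low.

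A reader might also infer that the PFS clock starts at diagnosis, which each arm reaches by a different route and possibly at a different time. The documents do not support that either. The next sentence of the Primary outcome section, the Discussion and the minimum follow-up rule all count from randomisation, so the reference to diagnosis is a slip in wording.

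What the reply does not remove is the conflict itself. A 2-year endpoint is named repeatedly across the article, and an analysis plan that chose one reading would still leave the published protocol inconsistent.

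**Conclusion.** The mismatch between the named endpoint and the basis of the sample size is established from the text, and it leaves the primary analysis open to two readings. Its numerical consequence is conditional. On a 2-year cut, the RC-alone set of 117 per group yields about 63 events and about 66% power in place of 88 and 80%, assuming constant event and censoring rates, which is the reading that reproduces 117. On the all-follow-up reading there is no shortfall, and the error lies in the label and in how the Discussion describes follow-up. Text has to change under either reading. The time-origin slip is minor and largely settled by the surrounding text.

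**What to change.** State one primary estimand that matches the test and the sample size: the PFS hazard ratio from randomisation, with all patients followed to the common cut-off already scheduled at month 66. Report Kaplan-Meier PFS at 2 years from randomisation as a supportive estimate. In the Primary outcome section, replace the reference to diagnosis with randomisation. In the Discussion, either correct the sentence on follow-up beyond 2 years or make clear that it concerns the minimum follow-up. Align the Abstract and Objectives with the chosen wording.

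If a 2-year horizon is truly intended, say so, truncate the analysis there, and restate the RC-alone events (about 63) and power (about 66%), or resize the trial (about 251 randomised per arm for 88 events in that set).

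The first option costs only wording in the protocol, and in the registry entry if it carries the same label (it was not seen). It needs no extra patients and no follow-up beyond what is already planned.
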